## Abstract

**Background:**

Internet based self-help for panic disorder (PD) has proven to be effective. However, studies so far have focussed on treating a full-blown disorder. Panic symptoms that do not meet DSM-IV criteria are more prevalent than the full-blown disorder and patients with sub-clinical panic symptoms are at risk of developing PD. This study is a randomised controlled trial aimed to evaluate an Internet based self-help intervention for sub-clinical and mild PD compared to a waiting list control group.

**Methods:**

Participants with mild or sub-clinical PD (N = 128) will be recruited in the general population. Severity of panic and anxiety symptoms are the primary outcome measures. Secondary outcomes include depressive symptoms, quality of life, loss of production and health care consumption. Assessments will take place on the Internet at baseline and three months after baseline.

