### Sample size

Power calculations are based on a moderate effect size of d=.50, comparing the PDSS-SR scores of the intervention group to the control group with a two-sided t-test (alpha .05, power 80%). To show this effect each group will consist of 64 participants [19], so the total sample size adds up to N = 128. Missing values will be imputed using regression imputation.

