#### Anxiety and panic symptoms

For severity of panic symptoms the Panic Disorder Severity Scale - Self Report (PDSS-SR) will be used. The PDSS is originally a face-to-face interview [24] and was adapted to self-report by Houck et al. [25]. The instrument contains seven items that assess the severity of seven dimensions of panic disorder and associated symptoms. The PDSS-SR generates a total score ranging from 0 to 28, with a higher score indicating more severe panic symptoms. The questionnaire has good psychometric properties with Cronbach's alpha = 0.92 and intraclass correlation coefficient = 0.81 [25]. In the current study, a score of 0-4 will count as no clinically relevant symptoms and 16 or higher as severe PD.

Anxiety symptoms in general will be measured with the Beck Anxiety Inventory (BAI) [26]. The BAI contains 21 short questions. Internal consistency is high, with Cronbach's alpha ranging from .90 to .94 [26]. The score varies from 0 to 63. A score of 30 or higher is interpreted as severe anxiety symptoms.

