## Discussion

Internet based self-help for PD has proven to be effective. However, existing interventions focus on treating a full-blown disorder, while sub-clinical PD is highly prevalent and can develop into full-blown PD. This study is a randomised controlled trial aimed to evaluate an Internet based self-help intervention for sub-clinical and mild PD compared to a waiting list control group. The primary outcome measure is the severity of panic and anxiety symptoms. Secondary outcome measures include depression, quality of life, loss of production and health care consumption.

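### Two outcomes are named primary (panic on the PDSS-SR, general anxiety on the BAI), but the trial is sized for the PDSS-SR alone and the document gives no rule for reading the two together

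*Protocol article*

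**What the plan says.** Two places in the protocol article define the primary outcome. The abstract (Methods) has: "Severity of panic and anxiety symptoms are the primary outcome measures". The Discussion has: "The primary outcome measure is the severity of panic and anxiety symptoms". Both name the same two constructs.

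The section Anxiety and panic symptoms gives each construct its own instrument and total score. For panic: "For severity of panic symptoms the Panic Disorder Severity Scale - Self Report (PDSS-SR) will be used", scored 0 to 28. For general anxiety: "Anxiety symptoms in general will be measured with the Beck Anxiety Inventory (BAI"), scored 0 to 63. No score combining the two is defined.

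The Sample size section uses one of them: "Power calculations are based on a moderate effect size of d=.50, comparing the PDSS-SR scores of the intervention group to the control group". It takes two-sided alpha .05 and 80% power, and concludes: "To show this effect each group will consist of 64 participants", so N = 128. No effect size, alpha or power is given for the BAI.

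The Analyses section applies linear mixed modelling to all outcomes, without an order of testing or a significance level. Methodological considerations hypothesises greater improvement on the outcome measures in general. The research question at the end of the Background concerns panic symptoms only.

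**The concern.** The definition of the primary outcome and the sample size do not match: two outcomes carry the primary label and one is powered. The text can be read in three ways. The PDSS-SR leads and the BAI supports it; either outcome suffices; or both are needed. Under the first reading the stated alpha and power describe the primary claim. Under the second, the error rate for that claim exceeds .05. Under the third, its power falls below 80%. If the PDSS-SR and the BAI disagreed at t1, a reader of this document could not tell whether the trial had met its primary objective.

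**Working it through.** **Inputs.** From Sample size: d = .50 on the PDSS-SR, two-sided alpha .05, power 80%, 64 per group. From Anxiety and panic symptoms: two separate scales. Assumed, because the document does not give them: the correlation ρ between the two test statistics, and, for joint power only, d = .50 on the BAI. All figures take 64 analysable participants per group.

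**1. The plan's own figure.** Two-sample t-test with n = 64 per group: df = 2 × 64 − 2 = 126, and non-centrality d√(n/2) = 0.5 × √32 = 2.83. The non-central t distribution gives power of 80.1%, and 64 is the smallest n per group that reaches 80%. The normal approximation gives 63 per group. The stated sample size reproduces for the PDSS-SR comparison.

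**2. Either outcome suffices, each tested at .05.** With independent statistics, the family-wise error is 1 − (1 − .05)² = 1 − .9025 = .0975. With correlated statistics, it is 1 − P(|Z₁| ≤ 1.96 and |Z₂| ≤ 1.96), where Z₁ and Z₂ are bivariate standard normal with correlation ρ:

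| ρ (assumed) | Family-wise error |
|---|---|
| 0 | 9.75% |
| 0.3 | 9.51% |
| 0.5 | 9.07% |
| 0.7 | 8.35% |
| 0.8 | 7.81% |
| 0.9 | 7.04% |

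Independence gives the largest value.

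**3. Both outcomes needed, each at .05.** The chance of wrongly claiming success does not exceed .05. Joint power by the normal approximation is P(Z₁ ≤ 2.83 − 1.96 and Z₂ ≤ 2.83 − 1.96), with d = .50 assumed on both scales:

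| ρ (assumed) | Joint power at 64 per group |
|---|---|
| 0 | 65.2% |
| 0.3 | 67.7% |
| 0.5 | 69.7% |
| 0.7 | 72.2% |

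**4. Alpha split equally (.025 each).** At 64 per group, power on the PDSS-SR is 71.2% (non-central t). Reaching 80% needs 78 per group, N = 156.

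**5. Fixed order, PDSS-SR first.** The PDSS-SR is tested at .05 with 80.1% power. The BAI is tested at .05 only after a significant PDSS-SR. If there is no effect on the PDSS-SR, any false claim requires a PDSS-SR rejection, which has probability at most .05. If there is an effect on the PDSS-SR but none on the BAI, a false BAI claim also has probability at most .05. The family-wise error for the two outcomes is therefore held at .05 whatever the correlation.

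**The case against.** A rule for multiple outcomes is something a condensed article may leave to the full protocol or the analysis plan, neither of which is shown. The lead outcome can also be inferred: the research question is about panic symptoms, and the PDSS-SR sets both eligibility and sample size. The first part stands to this extent: the absence of a rule here does not show that none exists. It does not remove the mismatch, because this article itself states both the primary outcomes and the sample size. The second part supports making the PDSS-SR the lead, but the abstract and the Discussion still give the BAI equal standing.

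Four stronger readings are tempting, and the document does not support them.

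- *The false-positive rate is nearly double the stated alpha.* That is the 9.75% reached only with independent statistics, and only if the BAI is also tested at .05 and either result counts. The document says neither. Two symptom scales completed by the same people are probably positively correlated, which lowers the figure.
- *The 80% power is wrong.* It is correct for the comparison it describes, and it stays correct for that comparison if both outcomes must succeed at .05. No joint power is claimed.
- *The abstract and the Discussion contradict each other because one is plural and the other singular.* The difference is only grammatical; the constructs are the same.
- *The choice of outcome will be made after the results are seen.* This article cannot establish that.

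**Conclusion.** The point holds as a mismatch within the stated text: two primary outcomes on two scales, one of them powered, and no order, split or either/both rule in the document. Its numerical effect is conditional on the rule adopted.

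- PDSS-SR leads: none; alpha .05 and power 80.1%.
- Either suffices at .05 each: family-wise error at most 9.75%, and about 9.1% to 7.0% for ρ from 0.5 to 0.9.
- Both needed: no inflation, with joint power of about 65% to 72% for ρ from 0 to 0.7.

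The correlations and the BAI effect size are assumptions. The mismatch itself does not depend on them. It is worth correcting because it concerns the headline claim and the correction is cheap.

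**What to change.** In the abstract and the Discussion, name the PDSS-SR total score at t1 as the primary outcome, in line with the research question and the Sample size section. State that the BAI is tested second, at two-sided .05, only if the PDSS-SR result is significant. The Sample size section needs no change on this point. The wording should be settled before t1 outcome data are examined.

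N stays at 128, PDSS-SR power is unaffected, and the error over the two outcomes is held at .05. The cost is that a significant BAI result without a significant PDSS-SR result can no longer support a positive primary conclusion.

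Other rules would also control the error. Requiring both outcomes would mean accepting, and stating, the lower joint power. Splitting alpha equally would need about 78 per group for 80% power at d = .50. Fixed order is the cheapest of the three and fits the existing sample size.

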**Discussion:**

Results will indicate the effectiveness of Internet based self-help for sub-clinical and mild PD. Strengths of this design are the external validity and the fact that it is almost completely conducted online.

**Trial registration:**

Netherlands Trial Register (NTR): NTR1639 The Netherlands Trial Register is part of the Dutch Cochrane Centre.

## Background

Anxiety disorders are highly prevalent, affecting one in six people during their lifetime [1], and cause a substantial loss of quality of life [2]. Direct and indirect costs caused by anxiety disorders are estimated at half a billion dollars per 1 million adults per year [3]. One of those anxiety disorders is panic disorder (PD). A study among the population in the Netherlands shows PD affects 1.5% of all adults each year, while 2% of the population is affected by sub-clinical PD [4]. Sub-clinical PD indicates infrequent panic attacks or frequent panic attacks that are relatively mild. It can be defined as panic symptoms that do not meet DSM-IV criteria for PD. Sub-clinical PD is a substantial burden for both the patient and society [4]. Panic symptoms are often comorbid with other mental health problems, like depression or other anxiety disorders [5]. Comorbid anxiety and depressive symptoms can lead to suicidal ideation [6] and PD elevates the risk at suicide attempts when comorbid with a mood disorder, substance abuse or another anxiety disorder [7].

While PD can be effectively treated by cognitive behavioural therapy and pharmacotherapy [8], it is known that only 25% of people with anxiety symptoms seeks help [9] and only 15% of people with panic symptoms receives effective treatment [10]. Help-seeking might be too difficult or fearful for people with panic symptoms, especially when they suffer from agoraphobia as well. In addition, help-seeking could be further compromised by fear of stigmatisation, misinterpretation of panic symptoms as a physical problem, or little awareness of effective treatment opportunities or available services.

A more accessible and perhaps more acceptable alternative to face-to-face interventions for PD is Internet based self-help. Several studies show promising effects of Internet based self-help for PD [11-13]. Moreover, Internet based self-help courses save clinicians' time and cost little compared to face-to-face treatment or pharmacotherapy [14].

Internet based self-help interventions for panic symptoms focus mainly on full-blown PD [11-13]. An accessible self-help course, tailored for the large group of sub-clinical and mild cases, would be beneficial to a group of patients that is not yet targeted by Internet interventions. Moreover, an Internet based self-help course for sub-clinical and mild panic symptoms could close the gap between prevention and early intervention of panic disorder.

This study is designed to evaluate Don't Panic Online (*Geen Paniek Online*) [15], an Internet based self-help course for sub-clinical and mild cases of PD with minimal guidance. Don't Panic Online (DPO) is based on Don't Panic (*Geen Paniek*) [16], a face-to-face group course for sub-clinical and mild panic symptoms. Don't Panic has proven to be cost-effective [17,18].

We will conduct a randomised controlled trial, comparing an experimental group that takes the course Don't Panic Online to a waiting list control group that will get access to an information website. The research question is the following: what is the effect of the Internet based self-help course Don't Panic Online on sub-clinical to mild panic symptoms?

## Methods

### Design

We will conduct a randomised controlled trial with two arms: (a) Internet based self-help with minimal guidance, (b) waiting list control group with information website. The Medical and Ethical Committee of VU Medical Centre approved the study protocol.

### Study population

The study population consists of adults with sub-clinical or mild PD. The inclusion criteria are the following: 18 years of age or older, Internet access, sub-clinical or mild PD (PDSS-SR score 5-15). Consequently, individuals with too mild (PDSS-SR score 1-4) or too severe (PDSS-SR score 15 or higher) panic symptoms will be excluded. Participants who report moderate to high suicide risk, as measured by a self-report version of the MINI, will be excluded as well. Applicants who report severe panic symptoms or suicide risk will be contacted by e-mail and advised to contact their general practitioner.

### Sample size

Power calculations are based on a moderate effect size of d=.50, comparing the PDSS-SR scores of the intervention group to the control group with a two-sided t-test (alpha .05, power 80%). To show this effect each group will consist of 64 participants [19], so the total sample size adds up to N = 128. Missing values will be imputed using regression imputation.

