### Intervention

Don't Panic Online (DPO) is an individual guided web-based self-help course, based on cognitive behavioural therapy. It was developed by the Trimbos Institute, which is the Netherlands Institute for Mental health and Addiction, in collaboration with GGNet, a Dutch mental health care institute. The course consists of six sessions, in which the participants will learn to control their panic symptoms by applying various cognitive behavioural techniques and skills. The course's format is based on Colour Your Life, an evidence based Internet intervention for depressive symptoms [20,21].

DPO is a protocolised treatment and consists of the following components: keeping a log of panic attacks; analysis of fearful situations; challenging thoughts that enable feelings of panic; replacing these thoughts by more realistic, constructive thoughts that reduce anxiety; behavioural exercises; and ranking exercises from manageable to difficult and carrying them out in order of difficulty. Each session consists of text, voice over, animated diagrams and video. A typical session will take about thirty minutes and consists of an introduction, a discussion of the previous lesson's homework, new theory and homework for the next week. The course is designed to be followed on a weekly basis until session five, while the sixth lesson can be followed four weeks after the fifth. The course can be completed in eight weeks.

Besides the lessons, the participant has several online resources at his or her disposal: a homework station, a panic attack log, a library for extra information, reading tips and a discussion board.

The DPO website contains an e-mail system for contact between a participant and a coach. For the current study, the coach will reply to questions about the course, its exercises and the participant's mental health. He will also contact the user weekly to ask after his progress. Participants will be supported for a maximum of three months. The coaches will consist of students who are in the final phase of their study of clinical psychology. All will receive a brief training.

Participants in the control group will receive access to DPO after completing the t1 measurement. In the mean time, they will have access to an information website about PD.

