### Analyses

Differences in demographic and baseline clinical characteristics will be computed with Chi-square tests, *t*-tests, and analysis of variance (ANOVA). The data of post-treatment measurements will be analysed in agreement with the intention to treat principle. Assuming missing data will be missing at random, the Linear Mixed Modeling (LMM) procedure will be used for all analyses to estimate missing values. LMM includes incomplete cases in the analysis and employs restricted maximum likelihood estimation to calculate parameter estimates.

Effects between the experimental and control group on continuous measures will be calculated with Cohen's *d*. Cohen's *d *is computed by subtracting the mean post-test score of the control group from the average score of the experimental group and dividing the difference by the pooled standard deviation. Effect sizes of 0.8 can be assumed to be large, while effect sizes of 0.5 are moderate, and effect sizes of 0.2 are small [35]. Estimated data from the LMM procedure will be used to analyse effect sizes.

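### The protocol states two missing-data methods, regression imputation and a REML mixed model, that cannot both govern the same missing t1 scores, and nothing reconciles them.

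*Protocol article*

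**What the plan says.** Two sections of the protocol article give a rule for missing data.

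- **Methods, Sample size.** After the calculation for a two-sided t-test on the PDSS-SR with 64 per group, the paragraph ends: "Missing values will be imputed using regression imputation". It gives no predictors, number of imputations or variance correction, and does not say which variables are meant.
- **Methods, Analyses.** "Assuming missing data will be missing at random, the Linear Mixed Modeling (LMM) procedure will be used for all analyses to estimate missing values". The section continues: "LMM includes incomplete cases in the analysis and employs restricted maximum likelihood estimation to calculate parameter estimates". On Cohen's d it adds: "Estimated data from the LMM procedure will be used to analyse effect sizes".

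Nothing assigns the two methods to different variables, separates missing items from missing assessments, or makes one primary and the other a sensitivity analysis.

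**The concern.** The two rules are different analyses. A likelihood-based LMM uses the scores that were observed and needs no filled-in values. Regression imputation replaces each missing score with a prediction. If t1 is imputed first, the LMM has no incomplete cases left at t1, so its stated way of handling them has nothing to act on.

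The position of the imputation sentence also matters. It directly follows a t-test calculation for 128 participants with no drop-out allowance, so it can be read as the means of keeping 128 analysable scores. If those scores are then treated as observed, either the reported precision or the estimated effect is wrong, depending on whether arm is in the imputation model.

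The sentence on effect sizes raises a related question. If its estimated data are predicted individual scores, the SD used for Cohen's d is too small.

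**Working it through.** **The plan's own figure.** Inputs from Sample size: d = 0.50, two-sided alpha 0.05, power 80%. The exact noncentral t gives power 0.795 at 63 per group and 0.801 at 64. The stated 64 per group reproduces.

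**Assumptions.** The document gives neither drop-out nor the t0–t1 correlation. I take a missing fraction p of 10–30% and a correlation ρ of 0.3–0.7, with n = 64 per arm, SD = 1, and t1 missing completely at random and equally by arm.

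**Case A: t1 imputed from t0 and arm, then analysed as observed by t-test.**

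- Variance of the filled-in scores within arm, which the t-test uses: V_rep = ρ² + (1 − ρ²)(1 − p).
- Quantity that drives the true variance of the difference: V_true = ρ² + (1 − ρ²)/(1 − p).
- Reported SE / true SE = √(V_rep / V_true).
- Type I error ≈ 2[1 − Φ(1.96 × that ratio)].

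At ρ = 0.5, p = 0.2: V_rep = 0.25 + 0.75 × 0.8 = 0.85 and V_true = 0.25 + 0.75/0.8 = 1.1875. The ratio is √0.716 = 0.85, and the type I error is about 9.7%.

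At ρ = 0.5, p = 0.3: V_rep = 0.775 and V_true = 1.321. The ratio is 0.77, and the type I error is about 13.3%.

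Simulation (8,000 trials per setting) agrees:

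| Missing | SE ratio, ρ = 0.5 | Type I error, ρ = 0.5 | Type I error, ρ from 0.7 to 0.3 |
|---|---|---|---|
| 10% | 0.92 | 6.8% | 6.2–7.2% |
| 20% | 0.84 | 10.1% | 7.9–11.3% |
| 30% | 0.76 | 13.4% | 10.3–15.3% |

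Repeat runs differed by up to about one percentage point. At 30% missing and ρ = 0.3, the type I error reached 16.7% when the number missing was left to chance. Adding one random residual to each imputed score does not cure this: the type I error was 9.6% at 20% missing and 11.9% at 30% (ρ = 0.5).

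**Case B: t1 imputed from t0 alone.** Imputed scores carry no arm difference, so the expected difference is 0.50 × (1 − p). That is 0.50 × 0.8 = 0.40 at 20% missing and 0.50 × 0.7 = 0.35 at 30%. Simulated type I error stayed near 5%. The fault is dilution and lost power, not false positives.

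**Case C: observed scores only.** A baseline-adjusted regression of observed t1, standing in for the likelihood-based LMM, gave a type I error of 4.6–5.4% and SE ratios of 0.98–1.01. This held across 10–40% missing and all three correlations.

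**Cohen's d from predicted scores (arm in the model, ρ = 0.5).** The pooled SD shrinks to √V_rep. A true 0.50 becomes about 0.50/√0.85 = 0.54 at 20% missing and 0.50/√0.775 = 0.57 at 30%. Simulated means were 0.55–0.56 and 0.57–0.58.

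**The case against.** The best defence is that the Analyses section governs. It is where analyses are specified, it applies the LMM to all of them, and it describes a sound likelihood method. The imputation sentence only closes a sample-size paragraph and names no analysis step. This stands: on that reading the primary p-value is unaffected. It does not remove the conflict, because the imputation sentence is unrestricted.

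Three stronger readings are tempting, and the document supports none of them.

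- **The trial's standard errors will be too small, or its 5% alpha fails.** This needs regression imputation to be applied to t1, arm to be in the imputation model, and the scores to be analysed as observed. None of these is stated, and with arm left out alpha holds. The text does not say that imputation is single, although it mentions neither multiple imputation nor a variance correction.
- **The method will be picked after seeing the data.** Nothing in the document indicates this.
- **Missing at random fails because only controls gain access by finishing t1** ("Participants in the control group will receive access to DPO after completing the t1 measurement"). Drop-out that differs by arm does not itself violate missing at random, since arm is observed and can be modelled. The experimental arm also has weekly coach contact, so the direction of any imbalance is unknown. A sensitivity analysis for this may sit in an analysis plan that is not shown.

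On Cohen's d, the phrase may mean model-estimated group means rather than individual predictions. In that case the inflation does not arise, but the wording leaves it open.

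**Conclusion.** The contradiction is in the current text and needs correcting. Its consequence is conditional. If the LMM governs, there is no harm to the primary test. If regression-imputed t1 scores are treated as observed, the outcome is wrong on either specification: alpha of roughly twice nominal at 20% missing with ρ = 0.5 when arm is in the imputation model, or an effect diluted by the missing fraction when it is not. These sizes rest on assumed drop-out and correlation and on data missing completely at random. At 10% missing the alpha inflation is small. The possible overstatement of Cohen's d is a separate, smaller point that would survive deletion of the imputation sentence.

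**What to change.** 1. Delete the regression-imputation sentence from Sample size, or limit it to a stated use that is not a whole missing t1 assessment.
2. In Analyses, name the likelihood-based LMM, with t0 and t1 as responses, as the only primary handling of missing t1 scores.
3. If imputation is kept as a secondary analysis, specify multiple imputation by arm with Rubin's rules. Lessons completed should not be used as an auxiliary variable for both arms, because the track-and-trace system logs them only in the intervention group.
4. State that Cohen's d is the LMM-estimated mean difference divided by an observed or model-based SD, not computed from filled-in individual scores.

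The cost is a few lines of protocol or analysis-plan wording, with no change to data collection or sample size. It should be done before any unblinded analysis.
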